#### Analysis of Outcomes

An intent-to-treat analysis, which will include all study participants based on participants’ arm allocation will be used. A random effects model will be used to estimate the effect of hydrotherapy by including time points (0 = baseline, 1 = follow-up) and participant ID as random effects to account for within-person correlation across time and between-person correlation. Participants lost to follow-up will be handled using single imputation procedures on the basis of the amount of missing and their distribution.

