**Methods:**

A sample of approximately 20 participants will be randomly assigned to either the intervention (hydrotherapy) or control group (standard physical therapy). Both interventions will be administered twice a week over a 9-week period (18 sessions in total). Primary outcomes are changes in neuropathic pain perception and pain catastrophization. Secondary outcomes are changes in disability and quality of life scores. They will be assessed at baseline and follow-up at 4 weeks after discharge. Validated Spanish language scales that will be used are the following: Numerical Pain Rating Scale, Pain Catastrophization, Health-related Quality of life, and the World Health Organization’s Disability Assessment Schedule 2.0. Generalized mixed linear models will be used for comparing baseline and postintervention means of each group and their differences, together with 95% CIs and *P* values. A *P* value of less than .05 will be considered significant.

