### Primary and Secondary Objectives

The main study hypothesis is that (1) hydrotherapy is effective in reducing NP in patients with SCI. Additionally, our secondary hypotheses are that (2) hydrotherapy decreases the catastrophization of neuropathic pain, and that (3) hydrotherapy improves life quality and minimizes the degree of disability, when compared to the other physical therapy techniques.

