#### Effectiveness of the Intervention

Treatment effects will be derived using longitudinal modeling of within-person change in mean scores of the scales and subscales’ scores from baseline to follow-up. Baseline characteristics of participants in both groups will be compared using the chi-square or 2-tailed Fisher exact test for categorical variables, and the Student *t* test or Wilcoxon test for continuous variables, after assessing the tests’ assumptions. Statistical significance will be set at a 2-tailed α of .05, expressed as a 95% CI.

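### The outcome model is written with two-level time as a random effect and no arm-by-time fixed effect, so as written it does not yield the promised between-arm difference in change

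*Protocol article*

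**What the plan says.** Three places in the protocol article describe the efficacy analysis.

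- **Analysis of Outcomes** gives the purpose, "A random effects model will be used to estimate the effect of hydrotherapy", and then the means, "by including time points (0 = baseline, 1 = follow-up) and participant ID as random effects". The reason given for these random effects is correlation within and between persons. Arm is mentioned in this section only to define the analysis set: "An intent-to-treat analysis, which will include all study participants based on participants’ arm allocation will be used".
- **Effectiveness of the Intervention** says "Treatment effects will be derived using longitudinal modeling of within-person change in mean scores", from baseline to follow-up.
- **Abstract, Methods** says "Generalized mixed linear models will be used for comparing baseline and postintervention means of each group and their differences", with 95% CIs and P values.

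Each participant is assessed twice. The Results section reports 18 participants, 10 in hydrotherapy and 8 in physical therapy.

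**The concern.** In a randomised comparison with one baseline and one follow-up score, the treatment effect lies in how the mean changes over time in one arm relative to the other. Time and arm must therefore both enter the mean part of the model, together with their interaction (or an equivalent baseline adjustment).

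The sentence under Analysis of Outcomes does something else. It puts time among the random effects, which treats baseline and follow-up as two draws from a population of occasions and estimates how variable such occasions are. It names no arm or arm-by-time term. The stated reason, correlation of scores within a person, is met by a random participant intercept alone. A random time effect adds only a shift shared by everyone measured on the same occasion.

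The effect estimate for the primary outcomes is therefore not pinned down. An analyst who follows the sentence gets no between-arm contrast. An analyst who repairs it by guesswork may get a diluted one. Two careful analysts could report different quantities under the same name.

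**Working it through.** The plan gives no effect size, SD or power figure, so there is no stated number to reproduce. The check concerns the structure of the model.

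**Inputs from the article:** 10 + 8 participants (Results); 2 assessments each, coded 0 and 1; random terms time and participant (Analysis of Outcomes).

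**Assumed inputs, for illustration only:** mean score 6, participant SD 1.5, residual SD 1.2, change of −1 in both arms, and an added hydrotherapy effect of 0, −2 or −4. The same random draw was used for all three effects.

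**1. The terms exactly as listed** (intercept, random time, random participant). There is one fixed-effect column, the intercept, and the likelihood does not involve arm. REML fits gave:

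| Added effect | Overall mean | Time variance | Residual variance |
|---|---|---|---|
| 0 | 5.33 | 0.27 | 0.96 |
| −2 | 4.77 | 1.71 | 2.01 |
| −4 | 4.22 | 4.35 | 3.92 |

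The overall mean moves only because 10 of the 36 scores are hydrotherapy follow-up scores: (10/36) × (−2) = −0.56 per step. The rest of the effect goes into the variances. There is no hydrotherapy-versus-physical-therapy estimate, CI or P value. The time variance itself rests on 2 − 1 = 1 degree of freedom.

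**2. The same terms plus an arm main effect only.** Let D0 and D1 be the between-arm differences in mean score at baseline and at follow-up. With both scores present for everyone, the arm coefficient is (D0 + D1)/2. Randomisation makes D0 zero in expectation, so the expected coefficient is D1/2. A true effect of −2 gives (0 − 2)/2 = −1, and −4 gives −2: half in each case. Chance imbalance at baseline moves the figure in a given trial.

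**3. Fixed time, arm and arm-by-time, with a random participant intercept.** There are 4 fixed-effect columns, of rank 4, so all are estimable with 18 participants and two times. With complete data the arm-by-time coefficient is D1 − D0, the between-arm difference in mean change. On the same simulated data:

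| Added effect | Arm-by-time coefficient (SE) | Difference in mean change, computed directly |
|---|---|---|
| 0 | −1.00 (0.63) | −1.00 |
| −2 | −3.00 (0.63) | −3.00 |
| −4 | −5.00 (0.63) | −5.00 |

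The coefficient follows the effect one for one. The constant −1.00 is sampling noise in the single draw used.

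**The case against.** The best defence is that the sentence describes the random part of the model and does not claim to list every fixed term. It says the model will estimate the effect of hydrotherapy. The abstract refers to mixed models "comparing baseline and postintervention means of each group and their differences", which implies arm and time in the mean structure. A condensed article may leave the full list of fixed effects to a longer document. All of this stands, and silence about arm would be a weak point by itself.

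It does not cover what is stated. Time is placed among the random effects, and that does not fit the comparison in the abstract. One can read the sentence so that only participant ID is random, but this is not its natural sense, and a plan should not depend on that reading.

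A reader might infer three stronger things that the documents do not support:

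- **That the plan has no between-arm parameter at all.** The abstract shows between-group intent, and unlisted fixed terms cannot be ruled out.
- **That efficacy will be judged by uncontrolled before-after tests.** Modelling within-person change is ordinary wording for change from baseline, which can be compared between arms. The main hypothesis, "hydrotherapy is effective in reducing NP in patients with SCI", names no comparator, but the design has parallel groups and an active control. No section plans to infer efficacy from significance in one arm, so false-positive rates for such tests would not measure this defect.
- **That the model cannot be identified.** This needs a participant-level random slope with its own covariance and a separate residual. The article specifies neither a slope nor a covariance.

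**Conclusion.** The point holds in limited form. The model sentence puts a two-level designed variable in the random part and names no arm-by-time fixed effect, so as written it does not deliver the between-arm difference in change that the abstract and the sentence itself promise. This is a stated misspecification, not merely missing detail.

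The size depends on how the sentence is carried out. Taken literally, it gives no between-arm estimate. With an arm main effect alone, it gives about half the true effect, assuming complete pairs of scores and no expected baseline difference. If the analyst in fact fits time, arm and their interaction as fixed effects, nothing is lost and only the text is wrong. The simulated values illustrate structure and say nothing about the effect to expect.

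Pilot status limits the consequences, since the article leaves conclusive answers to later trials. It does not remove them, because P values below .05 are to be called significant and the trial is meant to give preliminary evidence of efficacy.

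**What to change.** Replace the model sentence under Analysis of Outcomes with wording to this effect: each outcome is analysed with a linear mixed model with fixed effects for time, arm and arm-by-time and a random intercept for participant. The effect of hydrotherapy is the arm-by-time coefficient, that is, the between-arm difference in mean change from baseline to follow-up, reported with a 95% CI and small-sample degrees of freedom.

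An equally acceptable alternative is ANCOVA of the follow-up score on arm, adjusted for the baseline score. The arm coefficient is then the baseline-adjusted difference at follow-up. Choose one and name it. The two are different estimators, and in the mixed model the unadjusted difference at follow-up is the arm coefficient plus the arm-by-time coefficient, not the interaction alone.

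Add that within-arm changes are descriptive only, and align the abstract and Effectiveness of the Intervention with the chosen definition.

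The cost is a few lines of text and no new data. The change should be dated and made before the analyst sees results by arm.

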## Methods

### Trial Design

We will carry out a single-masked pilot trial of parallel groups in usual clinical practice conditions, with an allocation ratio of 1:1 (SPIRIT checklist in Multimedia Appendix 1 and the World Health Organization’s Trial Registration Data Set in Multimedia Appendix 2).

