### Statistical Analysis

#### Sample Size and Power Calculation

In order to demonstrate recruitment feasibility, 20 participants will be enrolled (10 per group) in accordance with sample size recommendations for pilot studies [53]. As this is a pilot study, power calculations were not performed.

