## Results

The first patient was enrolled in the study on March 30, 2019. The project timeline was changed owing to the COVID-19 pandemic and therefore delayed. Recruitment began in April 2019 and we recruited the final participants by December 2019. Figure 1 shows the flow diagram of the study. Participants were selected from the database of patients registered at the Spinal Trauma Clinic, Physical Medicine and Rehabilitation Unit of a Specialized Trauma Center [54]. We have collected information from 18 participants, including 10 in the hydrotherapy group and 8 in the physical therapy group. Results from the study will be disseminated via scientific publication, in ClinicalTrials.gov, and in national and international conferences in the second part of 2022. Authorship will be defined on the basis of the International Committee of Medical Journal Editors’ criteria for authorship. The authors do not have publication restrictions and will not use professional writers when reporting the results.

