### Limitations

This study has some limitations. Given the single-center design of our study, the generalizability of our results will be limited. Even though we have accounted for patients lost to follow-up, true percentages might be higher than expected, therefore skewing our findings. Despite the advantages of a single-masked trial design, double-masked trials are prone to less pitfalls [60].

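### An unnamed single imputation for lost follow-up scores can understate the standard error or bias the comparison, and the planned model does not need it

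*Protocol article*

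**What the plan says.** The Analysis of Outcomes section of the protocol article sets three things side by side. The analysis set is by allocation: "An intent-to-treat analysis, which will include all study participants based on" the arm each person was assigned to. The model is a random effects model with two time points per participant. Missing follow-up is dealt with in one sentence: "Participants lost to follow-up will be handled using single imputation procedures on the basis of the amount of missing and their distribution". No imputation type is named there, and no allowance for imputation uncertainty is mentioned.

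The preceding section, Effectiveness of the Intervention, fixes the decision rule: "Statistical significance will be set at a 2-tailed α of .05, expressed as a 95% CI". Sample Size and Power Calculation states that "20 participants will be enrolled (10 per group) in accordance with sample size recommendations for pilot studies", and adds: "As this is a pilot study, power calculations were not performed". The Results section reports the achieved numbers: "We have collected information from 18 participants, including 10 in the hydrotherapy group and 8 in the physical therapy group". No dropout rate appears anywhere. The Limitations section says only: "Even though we have accounted for patients lost to follow-up, true percentages might be higher than expected".

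**The concern.** Single imputation fills a missing follow-up score with one value and then forgets that it was invented. The model counts the person as fully observed, so the degrees of freedom and the nominal sample size are too large. If the filled value is taken from the participant's own arm, the residual spread is also usually too small. Confidence intervals are then too narrow and P<.05 occurs too often. With arms of 10 and 8, one imputed person is 10% or 12.5% of an arm, so a few losses matter.

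Other forms of single imputation fail differently. Carrying the baseline score forward sets that person's change to zero. If both arms improve and one loses more people, this creates a difference between arms that is not there.

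The step also brings no gain. A random effects model fitted by likelihood keeps participants who have only a baseline score and is valid when data are missing at random.

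**Working it through.** **Is there a figure to reproduce?** No. The target of 20 is 10 + 10 from a pilot-study recommendation, with no effect size, SD or power behind it. The only stated error rate is the nominal two-tailed 5%, so the check asks whether the imputation step preserves it.

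**Inputs from the protocol article.** Two-sided alpha 0.05; arms of 10 and 8 as achieved (10 and 10 as planned, "with an allocation ratio of 1:1"); two time points; random effects model of within-person change.

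**Assumptions.** Baseline-to-follow-up correlation 0.5; number missing 2 or 4 of 18, split equally between arms; missing completely at random; no true treatment difference. The first set of results also assumes no change over time. The model is read as a random-intercept model with a group-by-time effect. With complete (that is, filled-in) data and two time points, that test equals a two-sample t-test on change scores.

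**Closed-form check for one method.** Fill each missing change with the arm's mean change. Let n1, n2 be the arm sizes and m1, m2 the numbers observed. The estimate equals the observed-pairs difference, but the standard error is shrunk by

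ratio = sqrt{ [(m1+m2−2)/(n1+n2−2)] × [(1/n1+1/n2)/(1/m1+1/m2)] }

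and type I error = 2·P(t with m1+m2−2 df > t_crit × ratio), where t_crit on 16 df is 2.120.

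- 1 lost per arm (m = 9, 7): 14/16 = 0.875; 0.2250/0.2540 = 0.886; ratio = sqrt(0.775) = 0.880; 2·P(t14 > 1.867) = 8.3%.
- 2 lost per arm (m = 8, 6): 12/16 = 0.750; 0.2250/0.2917 = 0.771; ratio = sqrt(0.579) = 0.761; 2·P(t12 > 1.613) = 13.3%.

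The simulation below gives 8.4% and 13.5% for the same method.

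**Simulated type I error, arms 10 and 8, 20,000 trials per cell** (mean estimated SE / true SE in brackets):

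| Handling of missing scores | 2 of 18 missing | 4 of 18 missing |
|---|---|---|
| Arm mean | 6.0% (0.94) | 8.0% (0.87) |
| Arm regression | 7.4% (0.90) | 10.8% (0.80) |
| Arm regression plus random residual | 7.5% (0.90) | 10.2% (0.82) |
| Arm-mean change | 8.4% (0.86) | 13.5% (0.74) |
| Last value carried forward | 5.1% (0.97) | 4.4% (0.99) |
| Overall mean, both arms | 5.2% (0.98) | 4.9% (0.99) |
| Observed pairs only | 4.9% (0.98) | 5.3% (0.97) |

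Adding a random residual does not cure the arm-based methods. With the planned 10 and 10 and 4 missing, the four arm-based methods give 7.8% to 12.3%.

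**Last value carried forward when scores change.** Suppose both arms truly improve by the same amount D. The expected false difference is D × (fraction lost in one arm − fraction lost in the other).

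- None of 10 against 3 of 8 lost, D = 1 SD: 1 × 0.375 = 0.375 SD. Type I error was 11.1% to 11.7% in separate simulation runs (6.4% with D = 0.5 SD).
- None of 10 against 4 of 8 lost: false difference 0.25 SD (D = 0.5) or 0.50 SD (D = 1); type I error 8.5% or 18.0%.
- 2 lost in each arm: conservative, at 3.8% (D = 0.5) or 2.5% (D = 1).

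Observed pairs stayed at 4.8% to 5.1% in these settings.

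**The model without imputation.** REML random-intercept model, arms 10 and 8, 2 follow-ups missing per arm: with a t reference on 12 df, type I error was 4.7% (3,000 runs). With default large-sample z tests it was 7.4%, and 6.5% with 1 missing per arm (800 runs, simulation error about 0.9 points). The degrees of freedom therefore have to be part of the fix.

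**The case against.** The strongest reply is that the article names no imputation type and no dropout rate, so no inflated error rate can be read from it. That stands. A reader might infer that single imputation at this sample size necessarily gives false-positive rates well above 5%. The documents do not support that. Last value carried forward and overall-mean imputation are both single imputation, and both held about 5% under no change over time and loss completely at random. Inflation is driven by the fraction imputed and the method, not by sample size alone.

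A reader might also compute the inflation for arm-mean imputation from a t-test on follow-up scores only. With 2 of 10 lost per arm that gives an SE ratio of sqrt(7/9 × 8/10) = 0.789 and a type I error of 12.0%. This is not the planned analysis; under the change analysis the same imputation gives 7.8%.

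Three further replies limit the point. The Follow-up section has participants who withdraw from treatment invited at least three times by phone to answer the questionnaire, which should reduce missingness. The data analyst is masked to allocation, and choosing a method from the missingness pattern is not choosing it from the treatment effect; naming the procedure may also be left to an analysis plan that is not shown. And this is a pilot whose Conclusions leave definitive answers to later powered trials.

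What remains is that the article does commit to single imputation, beside a model that does not require it, with P<.05 as the significance rule. The safe behaviour of last value carried forward also depends on no change over time. Shared improvement is plausible, because both arms receive 18 sessions of active therapy.

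**Conclusion.** The point holds conditionally. The stated rule can give wrong error bars or a biased comparison, depending on which single imputation is chosen and how many follow-up scores are lost. For arm-based imputation, type I error is about 6% to 9% with 2 of 18 missing and about 8% to 14% with 4 of 18 missing, instead of 5%. For last value carried forward the fault is bias when scores change and loss is unequal between arms, not a small standard error.

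These sizes rest on assumed dropout, a correlation of 0.5 and loss completely at random. The article does not report how many follow-up scores are missing; if none are, nothing is affected. Neither the intention-to-treat statement nor the Limitations remark is a fault in itself. Severity is moderate: no confirmatory decision depends on this pilot, but its confidence intervals and P values will be reported and read.

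**What to change.** Delete single imputation from the primary analysis. State instead that the planned random effects model will be fitted by REML to all observed baseline and follow-up scores of every randomized participant, analysed by allocated arm, with small-sample degrees of freedom (for example Kenward-Roger or Satterthwaite). If a sensitivity analysis for missing data is wanted, use multiple imputation and fix its details before unmasking.

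The cost is about one sentence of analysis text and slightly wider confidence intervals. No further data are needed.

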## Results

The first patient was enrolled in the study on March 30, 2019. The project timeline was changed owing to the COVID-19 pandemic and therefore delayed. Recruitment began in April 2019 and we recruited the final participants by December 2019. Figure 1 shows the flow diagram of the study. Participants were selected from the database of patients registered at the Spinal Trauma Clinic, Physical Medicine and Rehabilitation Unit of a Specialized Trauma Center [54]. We have collected information from 18 participants, including 10 in the hydrotherapy group and 8 in the physical therapy group. Results from the study will be disseminated via scientific publication, in ClinicalTrials.gov, and in national and international conferences in the second part of 2022. Authorship will be defined on the basis of the International Committee of Medical Journal Editors’ criteria for authorship. The authors do not have publication restrictions and will not use professional writers when reporting the results.

**Figure 1 figure1:**
[figure not shown]
Flow of the study.

## Discussion

### Expected Findings

The expected main findings of this study are as follows: (1) effects on minimizing disability and improving quality of life between current standard and novel hydrotherapeutic approach are comparable; (2) hydrotherapy is a safe, efficient, and effective alternative to the current management of NP secondary to SCI; (3) given a choice, patients are more likely to choose hydrotherapy rather than the current standard of care if both options are presented to them. To our best knowledge, this is the first trial that proposes to evaluate the effects of hydrotherapy in the NP reduction in Latin America.

The purpose of rehabilitation is to maximize patients’ daily functional independence through a goal-oriented treatment [55]. Heterogenous results from previous hydrotherapeutic studies on patients with diabetic or other metabolic neuropathies do not allow for definitive conclusions [56]. Conversely, the hydrotherapeutic approach for patients with peripheral neuropathies has yielded positive results on gait and balance, which, besides pain, are the most commonly presented symptoms in our patient cohort [6,57].

The presence of a control group is necessary, since there are no currently available nonpharmacological treatments with evidence for NP management in patients with SCI. The pilot trial design with parallel groups aims to provide preliminary evidence on the clinical efficacy of hydrotherapy on NP secondary to SCI, with a single-masked study design being performed in order to alleviate bias. Consideration of a DN-4 score of ≥4 out of 10 for the identification of NP and mixed pain syndromes [39] ensures adequate screening in our trial population. This questionnaire has been suggested for epidemiological studies, where accurate identification of NP symptoms is also crucial to test in order improve therapeutic approaches.

Assessment of an alternative treatment to pharmacological management of neuropathic pain is reasonable, considering preclinical evidence on neuroendocrine changes facilitated by aquatic treatment, at the level of encephalin, corticotropins, endorphins, and prolactin, who are responsible for conduction of pain stimuli [58]. Accordingly, it may improve the prognosis of pain and its catastrophization [9,59]. Furthermore, this study will explore the evaluation of these therapeutic modalities, including variables related to perception and mental processes, which may affect the clinical condition and rehabilitation outcomes of these patients [46].

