### Data Management, Monitoring, and Auditing

The Steering Committee (SC) is formed by the team of researchers and presided by the principal investigator. It will meet on weekly basis to analyze the therapists’ clinical notes, which will be recorded after each session of therapy from both groups in order to verify participants’ attendance, their adaptation to therapy, adverse effects, contraindications, and clinical evolution. The follow-up survey (exit survey) will be scheduled 4 weeks after the end of the therapies in both groups. Participants will be assessed twice: in a baseline survey, and in a follow-up survey at the end of the interventions. To identify the survey as baseline or follow-up, the numbers “_0” or “_1” will be used at the end of the code of each survey to indicate the type of measurement. This database will be managed in accordance with the rules of security and confidentiality of the information, which govern the health care institution and Universidad del Valle. Any serious adverse event will be assessed and classified by the Data Safety Monitoring Committee. The trial will be ended using a *P* value of <.001 as a stop boundary. There will not be any interim analysis.

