### Ethics Approval

The study is endorsed by the Department of Physical Medicine and Rehabilitation, Hospital Universitario del Valle, Cali, Colombia. It was approved by the institutional review board of Universidad del Valle and Hospital Universitario del Valle (Internal Code 143-018/research ethics approval act 011-018). Additionally, the research complies with ethical standards of the Declaration of Helsinki; and in Colombia, it complies with the Ministry of Health resolution number 8430 of 1993. Since this study is considered to have “greater than minimum risk,” as it is a pilot trial where clinical interventions are conducted, there is, among other things, a risk of falls when entering and leaving the pool or a presence of fungal skin infections due to moisture. Before starting the medical evaluation, written informed consent for the study will be presented to participants by trained interviewers. These interviewers are not part of the medical assessment or randomization. Participants who agree to participate will sign the consent form, together with the required signatures of two witnesses (informed consent in Multimedia Appendix 11). Patient identities will be kept confidential, and an alphanumeric code will be used to identify each patient without enabling the distribution of personal data. The information that will be obtained in this study will be kept confidential, its use will be exclusive to the researchers, and disaggregated data will not be presented or used in a particular way that may lead to disclosure of confidential information, violation of any of the participants’ rights, or to the participants feeling stigmatized or discriminated against.

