### Conclusions

Hydrotherapy is likely to be a safe, efficient, and cost-effective alternative to the current standard of care for NP secondary to SCI, with comparable results between the two.

Since this is a pilot trial, randomized controlled trials with calculated power levels and sample sizes will be warranted in order to provide conclusive answers on noninferiority or superiority of the proposed treatment effect.

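### The article expects to conclude that hydrotherapy is safe, but no hypothesis, outcome or described analysis addresses safety, and 10 hydrotherapy participants cannot support that conclusion

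*Protocol article*

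**What the plan says.** Safety appears as a conclusion in three places in the protocol article.

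- **Discussion, Expected Findings:** the second expected main finding is that "hydrotherapy is a safe, efficient, and effective alternative to the current management of NP secondary to SCI". It carries no qualifier.
- **Discussion, Conclusions:** "Hydrotherapy is likely to be a safe, efficient, and cost-effective alternative to the current standard of care for NP secondary to SCI".
- **Abstract, Conclusions:** the same claim, also as a likelihood.

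The abstract gives the outcomes in two sentences: "Primary outcomes are changes in neuropathic pain perception and pain catastrophization" and "Secondary outcomes are changes in disability and quality of life scores". Table 1 lists the matching scales. Data Collection adds the ASIA impairment scale under the primary outcomes.

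Ethics Approval classes the study as above minimum risk and names "a risk of falls when entering and leaving the pool or a presence of fungal skin infections due to moisture".

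On monitoring, Interventions cites an adverse event report form (Multimedia Appendix 9). Data Management, Monitoring, and Auditing has the Steering Committee review session notes from both groups every week, adverse effects included, and adds: "Any serious adverse event will be assessed and classified by the Data Safety Monitoring Committee".

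On size, Sample Size and Power Calculation states "20 participants will be enrolled (10 per group) in accordance with sample size recommendations for pilot studies", for the purpose of showing that recruitment is feasible, and "As this is a pilot study, power calculations were not performed". Results reports 10 participants in hydrotherapy and 8 in physical therapy, with the last recruited by December 2019.

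**The concern.** An expected main finding should be something the design can confirm or fail to confirm. Here safety stands beside effectiveness as a headline result, but nothing in the stated hypotheses, outcomes or analyses leads to it. The sample was chosen to show recruitment feasibility, not to bound the risk of any harm.

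The article itself makes safety material, because it names harms tied to the pool. A reader planning the next trial, or offering pool therapy to people with spinal cord injury, could take a record with few or no events as confirming the announced conclusion. With 10 people exposed, such a record would say little about harms that are not very common.

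The article's own cautions do not cover this. The Discussion's Conclusions leave definitive answers to a powered trial, but only on whether the treatment effect is noninferior or superior. Limitations mentions neither sample size nor safety.

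**Working it through.** **Inputs**

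- Hydrotherapy participants: n = 10, both planned (Sample Size and Power Calculation) and obtained (Results).
- Control participants: 10 planned, 8 obtained.
- Two-sided α = .05 with 95% CIs (Effectiveness of the Intervention).
- Adverse event rate: none given. True risks of 5%, 10% and 20% are assumed below as a range.

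**The plan's own figure.** The sample size has no effect size, event rate or power behind it, so only the sums can be checked: 10 + 10 = 20 planned and 10 + 8 = 18 obtained. Both agree with the text.

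**Step 1: does any stated element address safety?**

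| Element | Content | Safety? |
|---|---|---|
| Hypotheses | Pain; catastrophization; quality of life and disability | No |
| Primary outcomes | NPRS and PCS (ASIA scale added in Data Collection) | No |
| Secondary outcomes | SF-36 and WHODAS 2.0 | No |
| Described analyses | Baseline comparisons; models of scale scores | No |
| Monitoring | Event form; weekly notes review in both groups; committee classification of serious events | Recorded and reviewed, but tied to no outcome or analysis |

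**Step 2: the most favourable record, 0 events in 10.** The exact (Clopper-Pearson) upper limit with no events solves (1 − p)^n = tail area.

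- Two-sided 95%: 1 − 0.025^(1/10) = 0.308, or 30.8%.
- One-sided 95%: 1 − 0.05^(1/10) = 0.259, or 25.9%.

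This step needs only n = 10 and no assumed rate.

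**Step 3: how often would a real harm go unseen?** P(no event in 10) = (1 − p)^10.

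| Assumed true risk | Calculation | Trials with no event |
|---|---|---|
| 5% | 0.95^10 = 0.599 | 60% |
| 10% | 0.90^10 = 0.349 | 35% |
| 20% | 0.80^10 = 0.107 | 11% |

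**Step 4: exposure needed for a zero-event record to exclude a given risk.** With a one-sided 95% limit, n is ln(0.05)/ln(1 − p) rounded up: 29 participants to exclude 10%, 59 to exclude 5% and 299 to exclude 1%.

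**Step 5: could a comparison of arms help?** Take 10 against 8 with no control events, and Fisher's exact test.

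- 4 of 10 with an event: [C(10,4) + C(8,4)]/C(18,4) = (210 + 70)/3060 = 0.092.
- 5 of 10 with an event: [C(10,5) + C(8,5)]/C(18,5) = (252 + 56)/8568 = 0.036.

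A two-sided difference at .05 would appear only if at least half the hydrotherapy arm had an event.

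**The case against.** The strongest reply has four parts.

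1. **Events are collected, and not only serious ones.** This stands. A reader might infer from the committee sentence that safety would be judged only on the absence of serious events in 10 people, with nothing known about the control arm. The article does not support that. The weekly review covers adverse effects in both groups without limiting them to serious ones, and a report form exists.

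2. **A journal article may leave the adverse event table to the full protocol or analysis plan.** This also stands. Neither document is shown, so the lack of a table or interval is not the point. The point is a conclusion that the article does state. No way of tabulating the events would let 10 participants establish it.

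3. **The wording is an expectation, not a decision rule.** This stands in part. Both Conclusions sections hedge, the trial is called a pilot, and its aim is described as preliminary evidence of efficacy. No planned test turns a clean record into a verdict. But Expected Findings has no hedge on safety, and the deferral to a powered trial leaves safety out.

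4. **The arithmetic holds for any arm of 10, and the 5%, 10% and 20% risks are assumed.** Both are true. The upper limits in Step 2 need no assumed rate, and their being generic does not make the stated conclusion attainable. Stating openly that no power calculation was done is proper for a pilot, but it argues against announcing safety.

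**Conclusion.** The point holds as a conclusion that the design cannot support. It is not a failure to collect adverse events. The most favourable possible record, 0 events in 10, leaves a true risk of up to 30.8% compatible with the data (25.9% one-sided). A harm affecting one participant in ten would go entirely unseen in 35% of such trials.

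The limits rest on n = 10 and on treating participants as independent, each counted once as having an event or not. The probabilities of seeing no event also rest on the assumed risks, which are not from the article.

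The pain, catastrophization, disability and quality-of-life analyses are unaffected. What needs to change is the safety claim and the reporting attached to it.

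**What to change.** 1. **Reword the safety claim** in the abstract's Conclusions, in Expected Findings and in the Discussion's Conclusions. Suggested text: *Adverse events in each group will be described; with about 10 participants per arm, the trial cannot establish the safety of hydrotherapy.* The article reports no outcome results, so the events observed belong in the results paper.

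2. **Report what is already recorded.** From the adverse event forms and session notes, give the number of randomized participants per arm with any adverse event, with falls and skin infection shown separately and with exact 95% CIs. Where a count is zero, print the upper limit beside it.

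3. **Label this as a descriptive outcome added after data collection.** Recruitment ended in December 2019 and information from 18 participants is already in hand.

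The cost is one extra descriptive table from existing records, some rewording and a weaker stated conclusion. No new data are needed, and the planned efficacy analyses do not change.
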